##### Curriculum program

An 8-week × 60-min HPE program based on the NSW K-6 syllabus [23] will be delivered during normal HPE lesson time [23]. The program is designed to improve the knowledge, skills and understanding of students in relation to HRF and also focuses on developing skills in assessing and monitoring HRF components. The program overview has been summarized in Table 1. The Fit-4-Fun program will be delivered by a member of the research team who is an experienced physical educator.

##### Family partnership

Children, their parents and family members will be provided with an 8-week home activity program designed to improve HRF levels using a range of engaging and enjoyable fitness activities, small-sided games and fitness challenges (3 × 20 min per week for 8 weeks). Children will select from a wide range of activities that are specifically designed to improve muscular fitness, flexibility and cardio-respiratory fitness. There are also goal setting activities and reflection tasks for students to complete with their parents throughout the program, enabling them to set personal fitness goals, monitor their achievement and to reflect on their progress.

##### School environment

Schools will be provided with activity task cards outlining the rules and organization of a range of fun and vigorous games (e.g. small-sided invasion games, skipping challenges) and a variety of equipment for use during break-times. The student directed break-time activities will involve participation in enjoyable games, activities and fitness challenges.

Social support for participation in all program activities will be provided by teachers, parents, and students throughout the intervention period. For example, teachers will verbally encourage students to join in the break-time games, there will be posters pinned at the exit points of the classroom reminding students to complete their home activities and to be active at lunch and recess, Fit-4-Fun leaders (students) will be asked to encourage other students to participate in activities and to make the equipment available for use, and parents will be asked to support and encourage their child at home. In addition, notices will be placed in the school newsletter and local media supporting the program and an incentive/award scheme for student participation will be in place. Students who complete home tasks and participate during curriculum sessions will be eligible to receive a gold, silver or bronze award.

The strategies used in the Fit-4-Fun program to target mediators of behaviour change are as follows:

##### Enjoyment

Many authors have argued that "fun" or enjoyment is considered one of the most important reasons that children and adolescents become involved and to continue to participate in physical activity - and a lack of fun or enjoyment is likely to lead them to withdraw [24,25]. Therefore, all of the programs components will involve participation in 'fun' and engaging physical activities, games, challenges or learning activities that children enjoy.

##### Self-efficacy

Self-efficacy is the central determinant of health behaviour change in SCT as self-efficacy beliefs directly and in-directly influence motivation, affect and behaviour [22,26]. Data suggest that there is a positive correlation between self-efficacy and the amount of vigorous physical activity in children and youth [27-29]. The techniques that are used in the Fit-4-Fun program and that have been shown to significantly improve physical activity self-efficacy, and therefore physical activity behaviours, include goal setting/action planning, positive reinforcement for effort or progress towards a set behaviour, the provision of instruction and feedback on performance, self-monitoring, self- regulation, the provision of information on consequences of behaviour and skills practice [30].

##### Supportive Environment

The school's social and physical environments are related to the facilitation or constraint of child and adolescent physical activity [31-34]. Strategies that have been implemented in the Fit-4-Fun program to improve the school and home environment include: increased access to play and sports equipment, provision of quality physical education lessons, and on-going positive reinforcement and *social support *from parents, teachers and peers [35-37].

#### Control (wait- list control group)

The control group will participate in their usual 60 min/week HPE lesson over the 8-week intervention period and will be delivered by their normal classroom teacher. The lesson content will be determined by the set school HPE program. The control group will receive the Fit-4-Fun program resources at the completion of the study period.

### Outcome measures

Demographic information (i.e., age, sex, language spoken at home, country of birth) and physical fitness cognitions (i.e., enjoyment, perceived social support, perceived environmental support, physical activity self-efficacy) will be collected via a questionnaire, and physiological data will be collected using the measures detailed below.

A battery of HRF field-based assessments will be conducted one week prior to intervention commencement. Field-based tests will be used as they provide an alternative to laboratory tests, since they are time efficient, cheaper, require fewer resources and can accommodate for multiple participants at once [38]. The testing environment will be identical for both baseline and follow-up measures and all tests, other than the beep test, will be performed in groups of three or four students with a trained research assistant remaining with the group for all assessments. The physiological fitness tests include:

#### Cardio-respiratory fitness (CRF)

##### 20 m shuttle run test (Beep test)

The participant will be required to run back and forth between two lines, 20 m apart, within a set time limit. Running speed will commence at 8.5 km/hr and will increase by 0.5 km/hr each minute using the 20 m Shuttle Run Test cadence CD. Participants will be instructed to run in a straight line, to place one foot over the 20 m line and to pace themselves according to the audio CD. The test requires maximal effort and participants are required to run until they can no longer keep up with the speed set by the tape. The level and number of shuttles within the level completed will be recorded [39].

#### Flexibility

##### Sit and reach test

Using standardized protocols as detailed in the FITNESSGRAM/ACTIVITYGRAM Reference Guide [40] the participant will perform the sit and reach test on the right leg, the left leg and both legs together. Double leg scores, followed by single leg (back saver) measures will be recorded in centimetres. A negative score on the sit and reach test indicates that the participant does not reach the level of the toes and a positive score indicates that the participant reaches beyond the level of the toes.

#### Muscular fitness (MF)

##### Standing jump [41,42]

The participant will be required to stand with both feet parallel and behind a marked starting line. The participant will be asked to swing their arms backwards and then forwards and to jump with both feet simultaneously as far forward as possible. Two attempts at the jump will be permitted with the furthest jump being recorded in meters. The distance measured is the distance between the starting line and the closest landing position (back of the heel).

##### 7- stage sit-up test [43]

The participant will lie on their back, with their knees at right angles and feet flat on the floor. The participant then attempts to perform one complete sit-up for each level in the manner prescribed below, starting at level 1. Each level is achieved if a single sit up is performed in the prescribed manner, without the feet coming off the floor. A second attempt is permitted if a level is not reached. The highest level sit-up correctly completed is recorded.

Level and Description:

0 = cannot perform level 1

1 = with arms extended, the athlete curls up so that the wrists reach the knees

2 = with arms extended, the athlete curls up so that the elbows reach the knees

3 = with the arms held together across abdominals, the athletes curls up so that the chest touches the thighs

4 = with the arms held across chest, holding the opposite shoulders, the athlete curls up so that the forearms touch the thighs

5 = with the hands held behind head, the athlete curls up so that the chest touches the thighs

6 = as per level 5, with a 5 lb (2.5 kg) weight held behind head, chest touching the thighs

7 = as per level 5, with a 10 lb (5 kg) weight held behind head, chest touching the thighs

##### Basketball throw test [44]

The participant sits on the floor with their buttocks, back, shoulders and head remaining against the wall and their legs straight with feet together. An assistant places a hoop on top of the participant's toes and the participant assumes the chest pass position with elbows touching the wall. The participant will perform a two-handed chest pass through the hoop and the distance from the wall to the ball's first point of contact on the ground is measured in metres (m). Each participant performs two trials.

##### Push-up test [40]

The participant will start in push-up position with their hands shoulder width apart and directly below their shoulders. Keeping the back and knees straight, the participant will lower the body until there is a 90-degree angle at the elbows, with the upper arms parallel to the floor, and then they will push back up to full extension of the arms. The push-ups will be performed in time to a metronome set at 40 beats per minute (bpm) and the participant will push-up on one beat and down on the next (20 push-ups per minute). The participant will continue until they can do no more in rhythm. The number of complete push-ups performed will be recorded.

#### Body composition

##### Height [44]

Height will be measured without shoes to the nearest 0.1 cm using the stretch stature method on a portable stadiometer (model no. PE087, Mentone Educational Centre, Australia). Height will be measures twice, with accepted values within 0.3 cm. A third measure will be taken if measures are not within the accepted range. The average of two acceptable measures will be reported.

##### Weight [44]

Weight will be measured to the nearest 0.1 kg in light clothing and without shoes using calibrated digital scales (Model no. UC-321PC, A&D Company Ltd, Tokyo Japan). Weight will be measures twice, with accepted values within 0.1 kg. A third measure will be taken if measures are not within the accepted range. The average of two acceptable measures will be reported.

##### Body Mass Index (BMI) [44]

BMI will be calculated using the formulae BMI = mass (kg)/height (m).2. Body mass index z-scores (BMIz) (measures of relative weight adjusted for child's age and sex) [45] will also be used to determine relative weight status based on international data [46].

#### Physical activity (PA)

The participant will be asked to wear a sealed Yamax SW700 pedometers (Yamax Corporation, Kumamoto City, Japan) during their normal daily activities to measure PA for seven days (including three consecutive days and one weekend day) [47]. This is a validated objective measure of physical activity for use with young people [48]. The participants will be asked to wear the pedometers at all times other than when sleeping or when they might get wet. Classroom teachers will record the step counts and then reset the pedometers of participants at the start of the school day (9 am) on Monday through to Friday during the assessment periods. On the weekend parents will be asked to record the step count readings of their child and to reset the pedometer as close to 9 am as possible. Any problems with recordings or participation in water-based activities are to be noted on the recording sheet and non-ambulatory activities are to be adjusted for on the daily step count via imputation. If imputation is required then a total of 1000 steps for 10 minutes of moderate -vigorous activity and 1500 steps for vigorous activity will be added to the participants step counts for the given time period [49].

#### Physical fitness testing experience and attitudes towards physical fitness testing

##### Student Questionnaire

The 'Fit 4 Fun' Student Questionnaire will be administered to participants at baseline, immediate post-intervention and 6-month follow-up and has been designed to collect information about the attitudes, opinions, behaviours and characteristics of the children involved in the Fit-4-Fun research project. The questionnaire design and purpose is described below.

*Demographic Information*: Six structured quick response questions will be used to determine the personal characteristics of the children participating in the study (age, DOB, school year, language, country of birth).

*Fitness testing experience*: Information relating to the participant's experience with fitness testing is sought through the use of five structured closed and semi-closed questions.

*Self-efficacy*: Information relating to participant's self-efficacy for PA will be measured using eight questions. The scale uses a single factor 5-point Likert format and is an adapted version of an 8-item questionnaire previously developed for use with 5th, 8th and 9th grade girls (PASES) [50-52]. The child is asked to select how much they agree with the eight statements by ticking the relevant circle ("Disagree a lot" though to "Agree a lot"). Each item is scored from 1 to 5, where a score of 1 indicates low self-efficacy. E.g. "I can be physically active even if it is hot or cold outside".

*Enjoyment*: of physical activity will be assessed through six negatively worded questions. The scale uses a 5-point Likert format and is an adapted version of the a 16-item version of the Physical Activity Enjoyment Scale (PACES) [53] and has been recently validated for use with children [54-56]. The child is asked to select how often they experience the relevant feeling about physical activity by ticking the relevant circle ("Never" though to "Every day"). Each item is scored from 1 to 5, where a score of 1 indicates low levels of enjoyment. E.g. When I am physically active........... It's no fun at all.

*Social Support for PA*: Children are required to indicate the level of social support for physical activity they receive from friends, family and teachers. The three scales use a 5-point Likert format and have been adapted from two scales used in the student survey of the Amherst Health and Activity Study [57]. Responses are sought for 3-items pertaining to social support from friends, 4 for social support from family and 4-items relating to social support provided by teachers. The structured scales use a 5-point Likert format and have been recently tested for validity and use with children by Dishman and colleagues (family and friend scales only) [55]. The teacher social support scale has been devised for the purpose of this study and follows the structure and wording of the other two scales. Children are asked to select how often a specific form of social support is provided to them during a typical week by ticking the relevant circle ("Never" though to "Every day"). Each item is scored from 1 to 5, where a score of 1 indicates low levels of social support. Scores are summed and then averaged, resulting in a scale mean. E.g. "During a typical week at school, how often do your FRIENDS.... do physical activity or play sports with you?"

*Perception of the School Physical Environment*: Information relating to the physical environment of the school is sought through 8 structured questions in part E of the questionnaire. The scale uses a single factor 4-point Likert format and is an adapted version of the 2-factor, 20-item questionnaire Q-SPACE developed by Robertson-Wilson, Levesque & Holden (2007). The child is asked to select how much they agree with the eight statements by ticking the relevant circle ("Strongly Disagree" though to "Strongly Agree"). Each item is scored from 1 to 4, where a score of 1 indicates a low level of support for physical activity in the school's physical environment (e.g. availability of equipment, play areas, supervision).

E.g. "There is sports equipment available for students to use during recess and lunch breaks"

*The School Environment Audit*: An audit will be completed by two independent research assistants to evaluate the school environment and its relationship to physical activity. The audit will use a purpose designed scale based on The School Environment Audit Tool [58] and the Physical Activity School Scan (PASS) [59]. The assessor will be asked to rate the quality and quantity of specific physical components of the school environment, including sport and play facilities, surrounding bike paths, playground design, aesthetics and sports equipment.

#### Process evaluation

The feasibility of the program will be examined using a number of strategies. Measures of recruitment (i.e., evaluation of the recruitment process, dissemination of information and obtaining informed consent), retention (i.e., how many students completed the program and participated in all assessments pre and post-intervention), adherence (i.e., the degree to which staff and students followed the Fit-4-Fun program), and satisfaction (i.e., level of satisfaction and engagement in the program by students, staff and parents) will be used. Evaluation questionnaires will also be administered to determine students' and teachers' perceptions of the various program components, attendance, and participation in extra-curricular activities. A 6-point Likert scale format will be used with responses ranging from "Strongly Disagree" through to "Strongly Agree" (e.g. "I think all schools should have the Fit-4-Fun Program"). Focus group interviews involving 2-3 students and lasting 5-10 minutes will also be conducted by trained research assistants to examine the perceptions of students about the Fit-4-Fun program. The groups will be based on friendship groups (both single-sex and mixed-sex groups) and will utilize standardized semi-structured questions. The anonymous verbal responses will be recorded by the research assistant. The following questions will be asked: What did you like about the Fit-4-Funprogram? What didn't you like about the Fit-4-Fun program? Did your activity levels change during the breaks at school/how? Were your parents/family interested/engaged in the home activities/how? How have your skills/attitudes/behaviours towards physical fitness changed over the past 8 weeks? How? What changes would you make to improve the program in the future? At the end of the session the participants will also be asked if they have anything else to add or would like to discuss anything further.

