**7**	Improving flexibility (practical)	• Revise flexibility and measuring flexibility • Participate in a practical PE lesson with a gross motor warm-up activity, dynamic stretches, fun stretching routines and cool-down • HR is monitored throughout the lesson • Discussion about the type of PA and improved flexibility	• Provide opportunity to participate in enjoyable physical activities in a supportive environment • Maximal participation is provided for and encouraged • Positive feedback is provided throughout the session • Students are to reflect on their performance and re-assess current PA behaviours • Link to lifelong behaviours	• Outcome expectations • Social support • Self-efficacy • Motivation

**8**	Improving health-related fitness through games (practical)	• Revise HRF components • Revise improving HRF • Participate in a student-centred practical PE lesson where students adapt fun games to incorporate HRF • HR is monitored throughout the lesson • Discussion about the type of PA and improved HRF • Summary of health benefits with improved HRF • Evaluation of 'Fit-4-Fun'	• Provide opportunity to participate in enjoyable physical activities in a supportive environment • Maximal participation is provided for and encouraged • Positive feedback is provided throughout the session • Students learn skills in adapting PA to improve HRF • Students are to reflect on their performance and re-assess current PA behaviours • Link to lifelong behaviours	• Outcome expectations • Self-efficacy • Social Support • Motivation

**1-8**	'Fit-4-Fun' Home Activities	• Participation in an 8 week home activity programme • 3 weekdays: MF, flexibility, CRF activities • 1 weekday: fitness assessments • Weekends: family activities & CRF assessment • Weeks 1, 5, 8: Goal setting tasks • Problem Solving Task (assessment)	• Students participate in a range of fun activities with their parents/siblings • Family provide social support throughout the programme • Students develop skills in self-monitoring and self-motivating • Students develop skills in goal setting & time management • Students develop skills in assessing & planning to improve the physical environment	• Outcome expectations • Self-efficacy • Social Support • Motivation

Abbreviations: SCT- Social Cognitive Theory; CMT - Competence Motivation Theory; HRF - Health-Related Fitness; HR - Heart rate;

CRF - Cardio-respiratory fitness; MF - Muscular fitness; PA- Physical activity

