## Discussion

The Fit-4-Fun study described in this paper is one of the first RCTs in Australia to specifically target the HRF levels of primary school children. The results of this study will provide further evidence to support the feasibility and efficacy of the Fit-4-Fun intervention for improving the HRF and PA levels of children, along with their attitudes towards physical fitness.

This study addresses some of the limitations found in previous interventions by: (1) specifically targeting all of the components of HRF in primary school children; (2) taking a multi-faceted approach to facilitating behaviour change via the HPS Framework; (3) having a theoretically- and curriculum-based program; (4) extending HRF education beyond the classroom and into the home; and (5) by using enjoyable and engaging learning activities to motivate students to adopt healthy behaviours.

The findings of this study will provide valuable information for other research groups looking to improve the HRF levels of children via school-based interventions. Furthermore, it will ascertain whether the Fit-4-Fun program is an effective program for future large-scale implementation.

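### One standardized focus-group question takes it for granted that the child changed, which can inflate themes of perceived change; it should ask whether before how

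*Protocol article*

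**What the plan says.** The Process evaluation section of the protocol article plans short focus groups of 2-3 friends, lasting 5-10 minutes and run by trained research assistants. The questions are described as standardized and semi-structured, the list is introduced as what will be asked, and the responses are recorded anonymously.

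Six questions are listed, followed by an open invitation to add anything. The fifth is "How have your skills/attitudes/behaviours towards physical fitness changed over the past 8 weeks", with a trailing one-word prompt, How. The third is "Did your activity levels change during the breaks at school/how". The fourth asks whether the family was interested or engaged in the home activities, again followed by how. The list also contains "What didn't you like about the Fit-4-Fun program" and "What changes would you make to improve the program in the future".

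The Statistical Methods section says these responses will be analysed inductively: quotes with similar meaning are grouped under a theme, and the themes are drawn as a concept map. The Discussion expects the study to give "further evidence to support the feasibility and efficacy of the Fit-4-Fun intervention", and mentions children's attitudes towards fitness among the things the results will speak to.

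**The concern.** A question that asks how something changed presupposes that it did change. A child who noticed nothing has to reject the premise of an adult's question, in front of one or two friends, to say so. Some children will do that. Others may offer something that fits the question.

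The analysis has no step that would remove such answers. It works from the content of the quotes, so an account of change prompted by the wording enters a theme on the same footing as a spontaneous one. The list is about the children's experience of the programme, and the article describes no parallel set of control-school answers against which a prompted theme could be seen. What is at stake is how far a qualitative finding that children felt their skills, attitudes or behaviours had changed can be taken at face value.

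**Working it through.** No arithmetic applies. The point depends on no sample size, variance, alpha or power, and the plan gives no figure to reproduce. The check is a reading of the six listed questions against each other.

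**Step 1: is the wording fixed?** Yes, as far as the article goes. It gives the questions in full and calls them standardized. The wording is therefore open to comment and is not a detail left to a fuller document.

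**Step 2: classify the six questions** (Process evaluation, in the order listed).

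| No. | Subject | Form |
|---|---|---|
| 1 | What was liked | Open, positive side |
| 2 | What was not liked | Open, negative side |
| 3 | Break-time activity | Whether it changed, then how |
| 4 | Family interest in home activities | Whether, then how |
| 5 | Skills, attitudes, behaviours | How they changed; whether is not asked |
| 6 | Improvements to the programme | Open, invites criticism |

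Questions 1 and 2 balance each other. Question 6 invites criticism. Questions 3 and 4 ask whether before how. Only question 5 presupposes that the child changed.

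**Step 3: was a neutral form available?** Yes. Question 3 also asks about change, and it begins by asking whether there was any. Question 5 departs from the pattern of its two immediate neighbours. Its trailing How also has no work to do as printed, because the question already opens with how. That prompt would make sense only after a question that asked whether.

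**Step 4: do the other questions repair it?** Only in part. Questions 2 and 6 let a child criticise the programme, but a child's opinion of the programme is a different matter from whether the child changed. Question 3 allows an answer of no change, but only for break-time activity. No other listed question asks whether skills, attitudes or behaviours in general stayed the same.

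**Step 5: how far does it reach?** The same section bases feasibility on recruitment, retention, adherence and satisfaction. Retention is a count of students who completed the programme and the assessments. None of recruitment, retention or adherence is described as depending on question 5. The Sample Size Calculation section names cardio-respiratory fitness as the primary outcome, and it is measured by the shuttle run. The reach is therefore the thematic analysis of the focus-group answers, and within it the themes of personal change.

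**The case against.** The strongest reply has four parts.

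- **It may be a drafting slip.** The redundant How suggests that the sentence was meant to open with Have. This is plausible. If so, the remedy is the same, because the sentence needs correcting before an interviewer reads it out.
- **No direction is stated.** A child could report a change for the worse. This stands, and it weakens any claim that the item is openly favourable. It does not remove the presupposition of change.
- **The format is semi-structured, and the interviewers are trained.** An interviewer may accept or prompt for no change. This may soften the effect, but the article describes no such prompt and calls the questions standardized.
- **The guide as a whole is balanced.** This stands. It asks for dislikes and improvements, puts the break-time question neutrally and closes with an open invitation. The fault lies in one question.

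Stronger readings are tempting, and the document does not support them.

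- **Evaluation in the deliverer's own lesson.** Table 1 lists "Evaluation of 'Fit-4-Fun" under week 8, and the Curriculum program section says "The Fit-4-Fun program will be delivered by a member of the research team who is an experienced physical educator". A reader might infer that children complete the evaluation questionnaires in front of the person whose programme they are rating. The table names no instrument, nothing links that entry to the questionnaires in the Process evaluation section, and the article does not say who administers those questionnaires or where. An article commonly leaves such detail to the full protocol. The focus groups themselves are assigned to research assistants.
- **Attendance as opinion.** The questionnaires are to determine "perceptions of the various program components, attendance, and participation in extra-curricular activities", and the format described is a 6-point agreement scale. A reader might infer that attendance will be known only as a rating. The text does not say that the scale covers attendance or that no roll is kept. Adherence is listed as a separate measure, and the award scheme in the School environment section depends on participation in the curriculum sessions.
- **All the feasibility evidence leans favourable.** One question cannot carry that conclusion when recruitment, retention and adherence are assessed separately.

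**Conclusion.** The point holds as a minor wording fault. One of the six listed questions presupposes change, a neutral form stands two lines above it in the same list, and the planned thematic analysis would not separate prompted from spontaneous reports of change.

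The direction of the effect is towards more themes of perceived change. Its size cannot be given: the article holds no data on how children answer, and how often a child would otherwise say that nothing changed is unknown. The conclusion assumes that the question is put as printed and that interviewers do not routinely ask first whether anything changed.

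It concerns secondary qualitative perception data only. It has no bearing on the shuttle-run outcome, the mixed-model analysis, or the recruitment, retention and adherence evidence. It should not be read as showing that the process evaluation as a whole is biased.

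**What to change.** Replace the question with one that asks whether before how and offers both answers, for example: *Over the past 8 weeks, have your skills, attitudes or behaviours in relation to physical fitness changed, or have they stayed the same? If they changed, how?* This brings it into line with the two questions that precede it. Answers that nothing changed should be kept as a group of their own when themes are formed, so that the balance between the two kinds of answer stays visible.

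The cost is one sentence in the interview guide and a mention in the research assistants' briefing. Nothing changes in the sample, the staffing, the quantitative outcomes or their analysis. The one drawback is that children who report no change will have less to say on this item.
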